##### Primary outcome analysis: degree of aggression regulation

2.7.1.2

An RM-ANCOVA will be conducted with the FSI-R scores at both pre- and post-intervention as the within-subjects factor. The treatment condition (Re-ART VR vs. regular Re-ART) will serve as the between-subjects factor. Covariates like age, motivation level, and risk of recidivism will be included to control for initial differences.

The primary focus will be on the interaction term between treatment condition and time to examine whether the rate of improvement in aggression regulation differs between the two conditions.

##### Secondary outcome analysis: cognitive biases and impulsivity

2.7.1.3

For secondary outcomes, separate RM-ANCOVA’s will be conducted for the BITI and the Impulsivity subscale of the FSI-R, using pre- and post-intervention scores as the within-subjects factors and treatment condition as the between-subjects factor. Additional covariates will be included as controls.

##### Moderators: patient and therapist motivation

2.7.1.4

To examine whether patient and therapist motivation moderate treatment outcomes, interaction terms between treatment condition and the respective motivation scales (MET scale of the TMS-F for patients and TMQ for therapists) will be included in the RM-ANCOVA models.

##### Sensitivity analyses

2.7.1.5

To assess the robustness of the results, sensitivity analyses will be performed to determine how the outcomes change when different covariates are included or excluded.

##### Correction for multiple comparisons

2.7.1.6

Given the multiple analyses conducted in this study, a correction for multiple comparisons will be applied to control the Type I error rate. We will use the Bonferroni correction method, which will adjust the alpha level accordingly.

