#### Sample size

2.3.1

To ensure sufficient statistical power for detecting significant effects in our repeated measures ANCOVA with within-between interaction, an *a priori* power analysis was conducted (G*Power; Faul et al., 2009). Using an expected effect size (f) of 0.25, a significance level (α) of 0.05, and a desired power (1-β) of 0.80, the calculation revealed that a total sample size of 34 participants is required for the study (17 in each condition). The analysis assumes two groups (Re-ART VR vs. regular Re-ART) with two measurement points (pre- and post-intervention), a correlation of 0.5 among repeated measures, and no sphericity correction (ε = 1).

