#### Statistical analyses

2.7.1

The data analysis will be conducted using IBM SPSS v29. The analytical plan aims to examine the effectiveness of Re-ART with VR (Re-ART VR) compared to standard Re-ART in a forensic outpatient setting. Intention to Treat (ITT) analyses as well as Per Protocol (PP) analyses will be conducted. The ITT analyses will include data from all randomized patients, regardless of drop-out, whereas PP analyses will include only those patients who completed the treatment as originally allocated.

To evaluate treatment effects on primary and secondary outcomes, a Repeated Measures Analysis of Covariance (RM-ANCOVA) will be performed. This approach allows to account for both baseline scores and time, along with other potential covariates, thus providing a more precise estimation of the intervention effect.

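### The sample size assumes an uncorrected alpha of 0.05, but the Bonferroni rule does not exempt the primary test; if that test is corrected, the stated 80% power is not reached

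*Protocol article*

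**What the plan says.** Section 2.3.1 (Sample size) bases the calculation on the within-between interaction of a repeated measures ANCOVA. It gives the effect size ("Using an expected effect size (f) of 0.25"), then "a significance level (α) of 0.05, and a desired power (1-β) of 0.80, the calculation revealed that a total sample size of 34" in total, 17 per condition. It also assumes two groups, two measurement points, a correlation of 0.5 between the repeated measures and no sphericity correction. Nothing there allows for multiplicity.

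Section 2.7.1.2 makes the treatment-by-time interaction on the FSI-R aggression regulation score the focus of the primary analysis. Section 2.7.1.3 adds separate models for two secondary outcomes, the BITI and FSI-R Impulsivity. Section 2.7.1.4 adds interaction terms for two moderators, patient and therapist motivation. Section 2.7.1 adds that "Intention to Treat (ITT) analyses as well as Per Protocol (PP) analyses will be conducted".

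Section 2.7.1.6 (Correction for multiple comparisons) gives the number of analyses in the study as the reason for controlling the type I error rate. It continues: "We will use the Bonferroni correction method, which will adjust the alpha level accordingly". It does not list the tests that share the alpha, say how many there are, or say whether the primary test is one of them.

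**The concern.** The article fixes two rules that bear on the same test. One sets the alpha for sizing the primary comparison at 0.05. The other lowers alpha because the study runs several analyses, and no section keeps the primary comparison at 0.05. If the second rule applies to the primary test, the power in section 2.3.1 describes a test that will not be carried out.

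Two things are at stake. First, the trial would be more likely to miss the effect it was designed to find. This differs from the limitation in section 3.2, which concerns effects smaller than the one assumed. Second, the primary decision threshold is left open. A primary p-value of 0.03 would be significant at 0.05, but not at 0.025 (two tests) or 0.0167 (three tests). The choice should not be open once results are known.

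**Working it through.** **Inputs, all from section 2.3.1:** f = 0.25; alpha = 0.05; target power 0.80; N = 34 (17 per arm); 2 groups; m = 2 measurements; correlation ρ = 0.5; ε = 1.

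**Formula.** For the within-between interaction in the G*Power parameterisation, the noncentrality is λ = f² × N × m / (1 − ρ). The degrees of freedom are (2 − 1)(2 − 1) = 1 and (N − 2)(2 − 1) = N − 2. Power is the probability that a noncentral F with these degrees of freedom and this λ exceeds the central F critical value at the chosen alpha.

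**Step 1: reproduce the plan's figure.** λ = 0.0625 × 34 × 2 / 0.5 = 8.5, with df 1 and 32. At alpha 0.05 the power is 80.7%. At N = 32 it is 78.1%, so 34 is the smallest even total that reaches 80%. The arithmetic in section 2.3.1 is correct, with little slack.

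**Step 2: divide alpha by k, with N and all other inputs unchanged.** The document does not state k, so each row below the first is conditional on a reading of section 2.7.1.6.

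| Tests sharing alpha (k) | Alpha for the primary test | Power at N = 34 | Total N for 80% power |
|---|---|---|---|
| 1 (primary test exempt) | 0.05 | 80.7% | 34 |
| 2 (smallest possible correction) | 0.025 | 71.2% | 42 |
| 3 (primary and two secondary outcomes) | 0.0167 | 65.2% | 46 |
| 5 (scenario: three outcomes and two moderators) | 0.01 | 57.5% | 52 |
| 6 (scenario: three outcomes, each ITT and PP) | 0.0083 | 54.7% | 54 |

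The first three rows carry the point. The last two show the direction for larger families and are assumptions.

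**Step 3: what this means.** With three tests, the chance of missing the assumed effect rises from 100 − 80.7 = 19.3% to 100 − 65.2 = 34.8%. Even k = 2 leaves power 80 − 71.2 = 8.8 points below target, so the shortfall does not depend on the exact divisor.

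**Step 4: checks.** The λ of 8.5 corresponds to a standardised difference in change scores of √(4 × 8.5 / 34) = 1.0. A two-sample normal approximation with 17 per arm gives 83.0% power at 0.05 and 69.9% at 0.0167. It runs a little higher than the F calculation, as expected in a small sample, and shows a drop of similar size. Spending three degrees of freedom on covariates changes any of the figures at N = 34 by less than one point. The document quantifies no gain in precision from covariates, so none was assumed.

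**The case against.** The strongest reply is that section 2.7.1.6 never says the primary test is corrected. The article separates one primary outcome from the secondary ones and sizes the trial at 0.05, so the authors may have meant the primary test to stay at 0.05. In that case 80.7% stands. This is possible, and it is why the conclusion is conditional. But the correction is tied to the study's analyses in general, and no section makes the exemption.

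A second reply is that the family and divisor are details a condensed article may leave to a fuller document. That holds for the details, and their absence is not the point. The point is that the article itself states both an alpha for sizing and a rule that changes alpha, and the two have not been reconciled.

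Third, Bonferroni is valid and conservative. It introduces no bias and does not inflate false positives, so any error here is towards a missed effect. Section 3.2 also already warns that 34 may be too few. Both remarks are fair. However, section 3.2 speaks only of small differences, repeats that the power analysis supports 34, and does not mention a corrected alpha.

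Three stronger readings are tempting but unsupported:

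- A reader might infer that every planned analysis is certainly corrected, so that 80% power is definitely lost. The text names no family and no divisor.
- A reader might multiply outcomes, moderators and ITT/PP versions into a large family and quote power near one half as the trial's power. The document does not show that moderator terms or per-protocol repeats are counted as members.
- A reader might say that precision is lost. Bonferroni moves the rejection threshold; the estimate, its standard error and a 95% interval do not change.

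**Conclusion.** The point holds in conditional form. Sections 2.3.1 and 2.7.1.6 use different alphas unless the primary test is exempt from the correction, and the document does not say that it is. If the primary test is in the family, power under the plan's own inputs falls from 80.7% to 71.2% with two tests and about 65% with the three named outcomes. It is lower still for larger families, but those figures rest on assumed divisors. If the primary test is exempt, the stated power is right and only the wording needs correcting. All figures assume f = 0.25, a correlation of 0.5 and complete data on 34 patients.

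**What to change.** **Preferred.** State in section 2.7.1.6 that the single primary test is the intention-to-treat time-by-condition interaction on the combined FSI-R Aggression and Anger score, tested at two-sided 0.05 without correction. Apply Bonferroni (0.05 / 2 = 0.025 each) or Holm only to the two secondary outcomes. Label the moderator and per-protocol analyses exploratory. Section 2.3.1 then stands as written. The cost is one paragraph of wording and no extra patients. The downside is that moderator and per-protocol results support only exploratory statements.

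**Alternative.** Keep the primary test in the corrected family, list the family, state the divisor, and restate the power in section 2.3.1: about 65% for three tests. This also needs no extra patients, but it means accepting lower stated power. Restoring 80% with three tests would take a total of 46, which is 46 − 34 = 12 more patients.

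Either choice should be recorded before outcome data are examined by condition.

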The primary objective of this Randomized Controlled Trial (RCT) is to assess the potential benefits of incorporating VR into the existing Re-ART. More specifically, the study aims to examine the extent to which VR enhances the degree of aggression regulation among aggressive forensic outpatients (Re-ART VR) above and beyond the effects found in their counterparts receiving the regular Re-ART intervention. The effect of cognitive biases and impulsivity as determinants of aggressive behavior is examined as secondary outcome measures as well. Moreover, the study will explore motivation as a moderating variable, both among patients undergoing treatment and among the therapists delivering the intervention. The hypothesis posits that patients treated with Re-ART VR will experience greater enhancements in the degree of aggression regulation, a more substantial reduction in cognitive biases and impulsivity compared to those receiving regular Re-ART. Additionally, it is expected that higher levels of patient motivation and therapist motivation will contribute to more pronounced improvements.

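### The plan fixes single-step Bonferroni, although Holm's step-down procedure controls the same error rate under the same conditions and never has less power

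*Protocol article*

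**What the plan says.** Section 2.7.1.6 states that "a correction for multiple comparisons will be applied to control the Type I error rate" and then names the method: "We will use the Bonferroni correction method, which will adjust the alpha level accordingly". A single adjusted alpha level is single-step Bonferroni: with m tests in the family, each is compared with alpha/m. No other purpose is given, and no simultaneous confidence intervals are planned. The section does not list the tests in the family.

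The candidates are in the preceding sections. Section 2.7.1.2 has one primary test, condition by time on the FSI-R aggression regulation score. Section 2.7.1.3 adds separate models that "will be conducted for the BITI and the Impulsivity subscale of the FSI-R". Section 2.7.1.4 adds two moderators, patient and therapist motivation.

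The Introduction expects Re-ART VR to do better on aggression regulation and also to give "a more substantial reduction in cognitive biases and impulsivity compared to those receiving regular Re-ART". Benefit is therefore hypothesised on all three outcomes.

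Section 2.3.1 sizes the trial at 34 patients (17 per arm) with an effect size f of 0.25, "a significance level (α) of 0.05" and "a desired power (1-β) of 0.80".

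**The concern.** Both procedures use the same p-values, the same family and the same overall alpha, and neither needs an assumption about the correlation between tests. Bonferroni keeps the strictest threshold for every test. Holm starts at that threshold and relaxes it after each rejection. If the plan wants only significance decisions with a controlled Type I error rate, the single-step form gives up power and gets nothing back.

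The cost depends on how many hypotheses in the family are false. When several outcomes truly respond, one rejection eases the threshold for the rest, and this trial hypothesises exactly that. With 34 patients, a real benefit on cognitive biases or impulsivity might be declared non-significant only because of the procedure chosen.

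**Working it through.** **1. Reproduce the planned power.** From section 2.3.1: N = 34, two groups, two measurements, f = 0.25, correlation between repeated measures 0.5, alpha = 0.05. For the within-between interaction the noncentrality is

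λ = N × 2 × f² / (1 − ρ) = 34 × 2 × 0.0625 / 0.5 = 8.5, with 1 and 32 degrees of freedom.

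Power is 0.807 at N = 34 and 0.781 at N = 32, so the stated 34 reproduces. The same case can be written as a t-test on change scores: a difference of 1.0 SD of change with 17 per arm gives λ = 1.0² × 17/2 = 8.5. The simulations below use this effect.

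**2. Compare the procedures.** Order the p-values p(1) ≤ … ≤ p(m).

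- Bonferroni rejects each hypothesis with p ≤ α/m.
- Holm compares p(1) with α/m, p(2) with α/(m−1), and so on up to α, and stops at the first failure.

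For m = 3, Bonferroni uses 0.0167 throughout; Holm uses 0.0167, 0.025 and 0.05. No Holm threshold is below α/m, so no Bonferroni rejection is lost. Error control: if m₀ hypotheses are true nulls, the first of them that Holm could reject meets a threshold of at most α/m₀. The chance that any of the m₀ true-null p-values falls that low is at most m₀ × α/m₀ = α, whatever the dependence.

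**3. Power if the hypothesised effects are real.** Simulated with 17 per arm, 1.0 SD of change on each true effect, and correlation between outcomes of 0.3 to 0.7. Family size and correlation are assumptions, because the article gives neither.

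| Family | Per true effect: Bonferroni | Per true effect: Holm | All shown: Bonferroni | All shown: Holm |
|---|---|---|---|---|
| Two secondary outcomes | 71% | 76–77% | 54–60% | 66–70% |
| Three outcomes | 65% | 73–74% | 35–46% | 56–64% |
| Five tests, three true effects | 57–58% | 61–62% | – | – |
| Five tests, all true effects | 57–58% | 67–69% | 15–30% | 41–54% |

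With three independent outcomes (correlation 0), the figures are 65% against 75% per outcome and 28% against 50% for all three.

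**4. Power if effects are weaker or isolated.** Correlation 0.5; the smaller effects are assumptions.

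| Setting | Bonferroni | Holm |
|---|---|---|
| m = 3, all effects 0.5 SD: each outcome | 16% | 19% |
| m = 3, all effects 0.3 SD: each outcome | 6% | 7% |
| m = 3, primary 1.0 SD, secondaries 0.5 SD: primary | 65% | 66% |
| Same setting: each secondary | 16% | 22% |
| m = 3, only the primary real: primary | 65.2% | 65.4% |
| m = 5, effects 1.0/0.5/0.5/0/0 SD: primary | 57% | 58% |
| Same setting: each secondary | 12% | 14% |

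**5. Error rate.** With no true effects the two procedures make a false rejection in exactly the same trials. Both had a family-wise error of 5.0% or less, within simulation error, for m = 3 and m = 5. With m = 3 and only the primary real, the error over the two true nulls was 3.0–3.4% for Bonferroni and 3.7–4.4% for Holm (correlation 0 to 0.7). Holm uses alpha that Bonferroni leaves unspent and stays below 5%. In every run Holm lost no Bonferroni rejection, and the chance of at least one rejection was identical.

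**The case against.** Bonferroni is valid and common, and it does what section 2.7.1.6 asks. Nothing there is contradictory, so this is a point about efficiency only. That stands.

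The large gains also need every outcome to respond at the full planning effect. The article's own limitations section doubts that 34 patients can detect small differences. With weak effects the gain is about 1–3 points per outcome, and with only the primary real about 0.2 points. Holm never adds a first rejection. That stands too, and it limits the size of the benefit.

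The family is not defined, so m and the number of true effects are assumed. This affects the figures but not the ordering, since Holm is at least as good for every m.

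Bonferroni gives simple matching simultaneous intervals, whereas Holm-adjusted p-values beside unadjusted intervals can appear to disagree. This is a real but small cost, because the article plans no simultaneous intervals.

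If the primary is pooled with the secondaries, Holm makes its verdict depend on theirs: a primary p of 0.03 passes only if both secondaries are rejected first. Bonferroni, however, would fail that primary outright.

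Finally, Holm does not repair the larger mismatch between a sample size set at unadjusted 0.05 and a corrected analysis. At N = 34, power per test under Bonferroni with m = 3 is 0.652; Holm reaches 73–75% at best, not 80%. That is a separate matter and gives no reason to keep the single-step form.

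**Conclusion.** The concern holds. For the one purpose the article states, single-step Bonferroni is dominated by Holm, whatever tests make up the family. The plan is valid as written, so this is a cheap improvement worth making rather than a correction of an error.

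Under the trial's own joint-benefit hypothesis, at the planning effect, with three tests and correlations of 0.3 to 0.7, Holm adds about 8–9 points of power per outcome. It adds about 17–21 points to the chance of showing all three benefits (63.7 − 46.3 = 17.4; 55.8 − 35.1 = 20.7). If effects are weak or confined to the primary outcome, the gain is small to negligible, but it is never negative.

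**What to change.** In section 2.7.1.6, replace the Bonferroni method with the Holm step-down (sequentially rejective Bonferroni) procedure, on the same family of tests at the same overall alpha of 0.05. Report Holm-adjusted p-values, that is, for the j-th smallest p-value the maximum over k ≤ j of min(1, (m − k + 1) × p(k)), beside the unadjusted estimates and confidence intervals. State that the intervals are not adjusted.

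The cost is one sentence. It needs no extra patients, data or software, since the adjustment follows from ordering the p-values. Simultaneous intervals become less simple, but none are planned. The change should be dated before outcome data are seen, because switching afterwards could look driven by the results.

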## Discussion

3

The main goal of this randomized controlled study is to evaluate the potential advantages of integrating VR into the existing Re-ART. VR is a relatively new technology in forensic outpatient treatment and preliminary evidence on its effectiveness has been provided only in forensic clinical samples (Klein Tuente et al., 2020). Based on the possibilities offered by VR (including being able to safely practice social skills in a role-playing game) and the opportunities to practice the learned skill in their own environment, it is plausible to assume that offering VR to forensic outpatients in addition to regular therapy will increase the treatment effect. To this end, an RCT-study has been set up to provide evidence for the added value of VR in enhancing aggression regulation skills in aggressive forensic outpatients (Re-ART VR) beyond the effects observed in those receiving the standard Re-ART intervention. Additionally, the research will explore motivation as a moderating factor, both among patients undergoing treatment and the therapists providing the intervention. It is expected that patients in the Re-ART VR-group will demonstrate a more significant improvement during the second assessment compared to patients in the regular condition, especially if both patients and therapists exhibit higher motivation levels. Including motivation as a moderator is a valuable addition because research shows that the lack of motivation in patients increases the chance of dropout, which in forensic patients eventually increases the chance of re-offending (Norcross et al., 2011).

### Study strengths

3.1

The randomized controlled trial (RCT) as described in the study protocol offers several strengths, chief among them the robustness inherent to its design. The RCT method is a gold standard in intervention research, providing a high level of internal validity. Another strength is the incorporation of VR as a novel modality for delivering Re-ART. Given the immersive capabilities of VR, this study could pave the way for more engaging and effective treatment regimes in forensic outpatients, a population that typically presents complex treatment needs. The use of VR also allows for a controlled, safe environment where patients can practice skills that would otherwise be risky to rehearse in real-life settings. Additionally, the study employs multiple outcome measures, including assessments of the degree of aggression regulation, cognitive biases and impulsivity, thereby providing a comprehensive evaluation of treatment effectiveness. The inclusion of both patient and therapist motivation as moderating variables is another crucial strength, recognizing the role that these factors play in treatment success.

### Potential limitations

3.2

While the study is designed with rigor, it is not without limitations. One limitation could be the sample size. Although power analyses suggest that 34 subjects will be adequate, this number may not be large enough to detect small but clinically significant differences between the two treatment modalities. This is particularly the case because the study focuses on a component of treatment rather than the entire intervention, and the issues faced by the target group are intractable. Another limitation is the potential for a novelty effect with the VR condition. Patients may initially be more motivated or engaged simply because the VR treatment is new and different, and this could potentially confound the results (Klein Tuente et al., 2020). Additionally, the study’s focus on adult male participants may limit the generalizability of the findings to broader forensic populations, such as females or adolescents. Furthermore, the limited duration of the intervention (3–6 months) and absence of follow-up measurement raises questions about the long-term sustainability of any observed treatment gains.

